# Effects of intraoperative PEEP optimization on postoperative pulmonary complications and the inflammatory response: study protocol for a randomized controlled trial

**DOI:** 10.1186/s13063-017-2116-z

**Published:** 2017-08-11

**Keywords:** Positive end-expiratory pressure, Static pulmonary compliance, Lung-protective ventilation, Radical cystectomy, Postoperative pulmonary complications, Procalcitonin

## Abstract

**Background:**

Patients undergoing general anesthesia and mechanical ventilation during major abdominal surgery commonly develop pulmonary atelectasis and/or hyperdistention of the lungs. Recent studies show benefits of lung-protective mechanical ventilation with the use of low tidal volumes, a moderate level of positive end-expiratory pressure (PEEP) and regular alveolar recruitment maneuvers during general anesthesia, even in patients with healthy lungs. The purpose of this clinical trial is to evaluate the effects of intraoperative lung-protective mechanical ventilation, using individualized PEEP values, on postoperative pulmonary complications and the inflammatory response.

**Methods/design:**

A total number of 40 patients with bladder cancer undergoing open radical cystectomy and urinary diversion (ileal conduit or orthotopic bladder substitute) will be enrolled and randomized into a study (SG) and a control group (CG). Standard lung-protective ventilation with a PEEP of 6 cmH_2_O will be applied in the CG and an optimal PEEP value determined during a static pulmonary compliance (Cstat)-directed PEEP titration procedure will be used in the SG. Low tidal volumes (6 mL/Kg ideal bodyweight) and a fraction of inspired oxygen of 0.5 will be applied in both groups. After surgery both groups will receive standard postoperative management. Primary endpoints are postoperative pulmonary complications and serum procalcitonin kinetics during and after surgery until the third postoperative day. Secondary and tertiary endpoints will be: organ dysfunction as monitored by the Sequential Organ Failure Assessment Score, in-hospital stay, 28-day and in-hospital mortality.

**Discussion:**

This trial will assess the possible benefits or disadvantages of an individualized lung-protective mechanical ventilation strategy during open radical cystectomy and urinary diversion regarding postoperative pulmonary complications and the inflammatory response.

**Trial registration:**

ClinicalTrials.gov, ID: NCT02931409. Registered on 5 October 2016.

**Electronic supplementary material:**

The online version of this article (doi:10.1186/s13063-017-2116-z) contains supplementary material, which is available to authorized users.

## Background

Patients undergoing general anesthesia and mechanical ventilation during major abdominal surgery commonly develop pulmonary atelectasis and/or hyperinflation of the lungs leading to complications either intraoperatively or in the postoperative period, resulting in ventilator-induced lung injury (VILI) [1, 2].

Lung-protective mechanical ventilation (LPV), by applying “low” tidal volumes (TV = 6 mL/Kg of ideal bodyweight, IBW), optimal positive end-expiratory pressure (PEEP) and regular alveolar recruitment maneuvers (ARM) in case of acute respiratory distress syndrome (ARDS) have been shown to be advantageous in critically ill patients. Recent studies have also shown positive results of LPV and regular ARM during general anesthesia in patients with healthy lungs [3, 4]. The main advantages of this strategy are improved gas exchange and prevention of either pulmonary atelectasis or VILI [5–7]. However, the effects of applying an optimal level of PEEP have not entirely been evaluated.

There are several types of PEEP titration methods such as dead space fraction (Vds/Vt)-guided or static pulmonary compliance (Cstat)-directed techniques [8–12].

Theoretically, in patients with healthy lungs, during general anesthesia and mechanical ventilation, inadequate PEEP values may lead to decreased pulmonary compliance and gas exchange disorders due to pulmonary atelectasis and/or hyperinflation of the lungs. In our clinical trial, optimal PEEP values will be determined during a static pulmonary compliance-directed PEEP titration procedure to protect from hyperdistention, and regular ARMs will be performed using the sustained airway pressure by the continuous positive airway pressure (CPAP) method, applying 30 cmH_2_O of PEEP for 30 s, to prevent atelectasis [5, 13, 14].

On the one hand major abdominal surgery induces an inflammatory response that is necessary for postoperative recovery (e.g., wound healing), but on the other hand an overwhelming inflammatory response may also lead to adverse events (AEs) such as organ dysfunction [15–19]. Radical cystectomy is considered major surgery; hence, there is an increased risk of postoperative complications. Inappropriate mechanical ventilation during general anesthesia can also lead to an amplified inflammatory response, which theoretically may worsen the postoperative outcome via several mechanisms. However, the relationship between LPV and the postoperative inflammatory response after radical cystectomy has not been investigated yet.

There is strong correlation between the degree of inflammatory response and serum procalcitonin (PCT) concentrations [20, 21]; hence, there is some rationale in the belief that monitoring the inflammatory response by regular PCT measurements in the postoperative period reflects the host response. Therefore, there is some rationale in monitoring PCT kinetics as an indicator of the host inflammatory response.

The aim of this investigator-initiated, double-center, single-blinded (subject), prospective, randomized controlled trial is to evaluate the effects of intraoperative LPV, applying an individually titrated optimal PEEP, on postoperative pulmonary complications (PPC) and the inflammatory response in patients undergoing radical cystectomy and urinary diversion (ileal conduit or orthotopic bladder substitute). We hypothesized that optimizing intraoperative mechanical ventilation (incorporating LPV, ideal PEEP and ARM) can attenuate the inflammatory response as compared to conventional modes of mechanical ventilation, and hence may result in improved postoperative oxygenation, prevent the occurrence of VILI, and reduce the incidence of organ dysfunction. These anticipated advantages may also improve postoperative recovery and survival rates, shorten in-hospital stay and reduce health care-related costs.

## Methods/design

### Objectives of the study

The main objectives of this trial are to compare the effects of a standard LPV applying 6 cmH_2_O of PEEP to a LPV using an individually titrated optimal PEEP on: (1) oxygenation and PPC, (2) the degree of inflammatory response evaluated by early PCT kinetics (0, 2, 6, 12, 24, 48 and 72 h after surgical incision) and (3) to evaluate the relationship between the degree of inflammation and postoperative pulmonary and extrapulmonary complications.

### Study endpoints

The primary outcome variables are PPC and PCT kinetics. PPC are defined as new infiltrates or atelectasis on a chest X-ray, abnormal breathing sounds on auscultation, respiratory failure defined as PaO_2_/FiO_2_ < 300 or the need for noninvasive or invasive ventilatory support within the first three postoperative days. PCT kinetics will be evaluated during and after surgery. Blood samples will be taken at 0, 2, 6, 12, 24, 48 and 72 h after surgical incision. According to recent data it is expected that PCT values will peak at approximately 24 h after surgery and that they should decline by approximately 50% daily in the case of an uneventful postoperative course. Therefore, in addition to the absolute values the change between T_0_–T_24_–T_48_ will also be evaluated [16, 22].

Secondary outcome variables are extrapulmonary complications: incidence of circulatory failure, gastrointestinal and renal dysfunction, hematologic and coagulation disorders and infection (Table 1).

**Table 1 Tab1:** Secondary endpoints

Endpoint	Time frame	Detailed description
Circulatory failure	28 days	Hypotension – MAP < 65 mmHg
		Severe cardiac arrhythmia – 40/min < HR > 150/min
		ScvO_2_ < 70%
		dCO_2_ > 7 mmHg
		Serum lactate > 2 mmol/L
		Severe metabolic acidosis (actual bicarbonate < 18 mmol/L)
		Acute coronary syndrome
		Acute left ventricular failure
		Pulmonary embolism
		Cardiac arrest
Gastrointestinal dysfunction	28 days	Constipation
		Ileus
		Anastomotic leakage
		Reoperation
		Disorders of liver function
Renal dysfunction	28 days	RIFLE criteria
Hematologic and coagulation disorders	28 days	Severe bleeding
		Coagulopathy – INR > 1.5
Infection	28 days	Any infection except from pneumonia

*MAP* mean arterial pressure, *HR* heart rate, *ScvO*
_*2*_ central venous oxygen saturation, *dCO*
_*2*_ central venous-to-arterial carbon dioxide gap, *INR* International Normalized Ratio

Tertiary endpoints are intensive care unit (ICU) days, in-hospital stay, in-hospital and 28-day mortality.

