### Statistics

Data will be analyzed by the research team in collaboration with a medically versed biostatistician after completion of the trial. There will be no interim analysis. Statistical analysis will be conducted on an intention-to-treat basis. IBM SPSS 20.0 statistical software will be used for analysis.

It is expected that the majority of source data will be recorded onto CRF; nonetheless, before starting the data analysis, the mechanism and pattern of missing data will be evaluated and these findings will be used to determine whether they have had an impact on the statistical analysis and results and how they can be managed.

Data distribution will be tested by the Kolmogorov-Smirnov analysis. Normally distributed data will be presented as mean and standard deviation (SD) and skewed data as median (interquartile range). Comparing related samples, the paired and unpaired *t* test will be used for normally distributed data and the Wilcoxon signed rank test and Mann-Whitney *U* test for skewed data. Differences in proportions will be evaluated using the Fisher’s exact test, and risk ratio with associated 95% confidence interval (CI). Analysis of the primary endpoint (PPC) will be carried out by the unpaired Student’s *t* test (95% CI). A two-way, repeated-measures analysis of variance (two-way RM ANOVA) will be used to compare the groups’ serum PCT levels. The relationship between PCT levels and organ dysfunctions will be evaluated using the Pearson correlation. Statistical analysis of SOFA scores, ICU days, in-hospital stay, in-hospital and 28-day mortality data of groups will be implemented by the chi-square test. A *P* value < 0.05 will be considered significant.

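### The protocol names two primary outcomes in one place and one in another, tests everything at P < 0.05, and does not say which result decides the trial

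*Protocol article*

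**What the plan says.** The Abstract (Methods/design) uses the plural: "Primary endpoints are postoperative pulmonary complications and serum procalcitonin kinetics during and after surgery until the third postoperative day". Study endpoints repeats it: "The primary outcome variables are PPC and PCT kinetics". For PCT, the same section sets out the sampling: "Blood samples will be taken at 0, 2, 6, 12, 24, 48 and 72 h after surgical incision". It then adds that, "in addition to the absolute values the change between" baseline, 24 h and 48 h will be examined.

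The Statistics section uses the singular: "Analysis of the primary endpoint (PPC) will be carried out by the unpaired" t test. The next sentence assigns group PCT levels to a two-way repeated-measures ANOVA, without calling PCT primary and without saying whether the group effect or the group-by-time effect is the one that counts. The section closes with one threshold for all tests: a P "value < 0.05 will be considered significant". It gives no split of alpha, no testing order and no requirement that both outcomes succeed. It also rules out interim analyses, so no alpha is spent on early looks.

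**The concern.** A reader of the final report needs to know which result makes the trial positive. The Abstract and Study endpoints give two candidates; Statistics gives one. If both are primary and either is enough, testing each at 0.05 takes the chance of a false positive primary claim above 5%. Leaving the deciding PCT contrast open adds further routes to a positive claim. The plan describes only participants as blinded, has the research team analyse the data together with a biostatistician, and expects positive results to apply to similar major abdominal surgery. The choice of headline result should therefore be fixed before the data are examined.

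**Working it through.** **Inputs from the protocol article.** Two primary outcomes (Abstract, Study endpoints); one primary endpoint (Statistics); P < 0.05 per test (Statistics); 40 patients randomized 1:1, so 20 per arm; seven PCT times; changes across T0, T24 and T48 in addition to levels. The protocol gives no effect size, SD, PPC rate, power or overall error rate, so it has no figure of its own to reproduce.

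**Assumptions.** Two-sided tests; PPC analysed as yes/no; correlations and PPC rates as shown below.

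**Step 1: two tests, either sufficient.** For independent tests the overall rate is 1 − (1 − α₁)(1 − α₂). With both at 0.05 this is 1 − 0.95² = 0.0975. For correlated tests (bivariate normal):

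| Correlation | Overall rate |
|---|---|
| 0 | 9.75% |
| 0.3 | 9.5% |
| 0.5 | 9.1% |
| 0.8 | 7.8% |

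**Step 2: actual size of the PPC test.** Exact enumeration at 20 per arm, for true PPC rates of 10% to 50%, combined with an independent PCT test at 0.05:

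- *t test on 0/1 data (the named method):* size 3.9% to 5.3%, overall 8.7% to 10.1%. The highest value, at a PPC rate of 30%, is 1 − (1 − 0.0533)(0.95) = 0.1006.
- *Fisher's exact test (named in Statistics for proportions):* size 1.2% to 2.5%, overall from 1 − (1 − 0.0118)(0.95) = 0.0612 to 1 − (1 − 0.0248)(0.95) = 0.0736.

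**Step 3: either ANOVA effect may count for PCT (three tests).** If independent, 1 − 0.95³ = 14.3%. Simulations under no effect gave 13.2% (3,000 trials; between-patient log SD 0.8, within-patient 0.5) and 15.2% and 17.3% (20,000 trials each; autoregressive correlation 0.3 and 0.7, PPC rate 30%, no sphericity correction). Part of the 17.3% comes from the uncorrected interaction test, whose own size was 8.3% at correlation 0.7.

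**Step 4: the T0–T24 and T24–T48 changes also count (five tests).** If independent, 1 − 0.95⁵ = 22.6%. The 20,000-trial simulations gave 21.4% and 22.4%.

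**Step 5: readings without inflation.** If PPC alone is primary, the rate is the size of the PPC test, 3.9% to 5.3% for the t test. If both outcomes must be significant, the rate cannot exceed the 0.05 of either test; with no effect on either outcome and independent tests it is 0.05 × 0.05 = 0.0025.

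**Step 6: price of control.** The standardized difference detectable with 80% power at 20 per arm (normal approximation) is (z₁₋α/₂ + z₀.₈₀) × √(2/20). At α = 0.05 it is (1.960 + 0.842) × 0.3162 = 0.886. At α = 0.025 it is (2.241 + 0.842) × 0.3162 = 0.975. Power for a difference of 0.886 SD falls from 80% to 71%. Holding 80% would take 1.211 times the sample, or 25 instead of 20 per arm.

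**The case against.** Four points can be made for the plan.

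First, it states no rule for success, so inflation is not written into it. This stands. A reader might infer that any single PCT contrast below 0.05 supports a positive primary claim, but no sentence says so. Nor does the protocol promise a familywise 5% that it then breaks; 0.05 is a per-test threshold. The inflated figures are conditional.

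Second, seven sampling times do not mean seven tests. This also stands. Statistics names one global ANOVA for group PCT levels, and the mention of absolute values in Study endpoints separates levels from changes without announcing a test at each time. Adding six time-point comparisons yields about 28%, but that rests on tests the plan does not schedule and on one assumed SD setting. It is not part of this point.

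Third, a multiplicity procedure is commonly left to an analysis plan, and an article condenses the full protocol. That is fair for the procedure and the choice of ANOVA effect. It does not remove the mismatch within the article over how many primary endpoints there are.

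Fourth, the parenthesis in Statistics may only identify which of two primaries is being discussed, since PCT follows in the next sentence. The reading is possible, but it leaves two primaries at 0.05 each with no statement of whether one or both decide. The opposite reading, PCT as secondary, sits badly with the rest of the article: PCT is among the main objectives, the hypothesis in Background starts from the inflammatory response, and the secondary outcomes listed are extrapulmonary complications only.

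**Conclusion.** The point holds as an internal conflict together with a missing decision rule. Whichever reading is intended, at least one section needs an edit or a clarification. The consequence depends on the rule adopted: about 6% to 10% if either outcome suffices, about 13% to 17% with a free choice of ANOVA effect, about 21% to 22% with the two changes as well, and about 5% or below if PPC alone is primary or both must succeed. These ranges rest on two-sided tests, a binary PPC outcome, and assumed correlations and PPC rates. The two-test range also depends on whether the t test or Fisher's test is used for PPC. The documents do not support saying that the trial's error rate is inflated on every reading.

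**What to change.** Reconcile the Abstract, Study endpoints and Statistics before the final analysis, in one of two ways:

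1. Name PPC as the sole primary outcome and PCT kinetics as secondary.
2. Keep both as primary and test them by Holm at a familywise two-sided 0.05, which is valid under any dependence between them.

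Under option 2, designate one test from the planned repeated-measures analysis, for example the group-by-time effect, as the primary PCT test. Under either option, label the T0–T24–T48 changes and any time-point comparisons as supportive. The ANOVA need not be replaced to settle this point.

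The text change is a few sentences. Option 1 costs no alpha, but it changes an endpoint's status in a trial reported as ongoing, so it should be dated and made without sight of results by group. Under option 2 the smaller P value must be below 0.025, and the other is then tested at 0.05. The power loss in step 6 is for a fixed 0.025 on each outcome, so it is the most that Holm can cost: detectable difference from about 0.89 to 0.97 SD, or power for 0.89 SD from 80% to about 71%.

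### Two primary outcomes are named, Statistics labels only PPC as primary, and no rule links the two tests; if either may count, the false-positive chance could reach about 9.75%

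*Protocol article*

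**What the plan says.** Two places give the trial two primary outcomes. Study endpoints says "The primary outcome variables are PPC and PCT kinetics". The Abstract says "Primary endpoints are postoperative pulmonary complications and serum procalcitonin kinetics during and after surgery until the third postoperative day".

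The Statistics section is worded differently. For PPC it says "Analysis of the primary endpoint (PPC) will be carried out by the unpaired Student’s" *t* test. The next sentence assigns PCT a two-way repeated-measures ANOVA that "will be used to compare the groups’ serum PCT levels", without calling it primary. A single threshold then covers all tests: a *P* "value < 0.05 will be considered significant". No split of the 5%, testing order or both-must-succeed rule is given.

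Study endpoints also attaches more than one analysis to PCT: "in addition to the absolute values the change between T_0_–T_24_–T_48_ will also be evaluated".

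No sequential testing adds to the problem, because "There will be no interim analysis".

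**The concern.** A trial with two primary outcomes needs a rule that turns two *P* values into one conclusion. Here the endpoint text and the analysis text do not agree on how many primary outcomes there are, and the one decision rule that is stated is applied to each test separately.

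Two things are at stake. The first is the error rate behind the primary claim: 5% applies to each test, but not to a claim that either test may support. The second is interpretation of a split result. If PPC shows no difference and PCT does, an author following the Abstract and Study endpoints could report a positive primary outcome. An author following Statistics would have to report a negative one. With 40 patients such a split is quite possible, and the choice should not be open once the results are known.

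**Working it through.** **Inputs from the article**
- Primary outcomes: 2 (Abstract; Study endpoints). Primary endpoints named in Statistics: 1 (PPC).
- Threshold: 0.05 for each test. Sidedness is not stated; two-sided is assumed.
- 40 patients randomised 1:1, so 20 per arm.
- Interim looks: none.

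**Assumptions, because the article gives no figure**
- Correlation between the two test statistics: 0 to 0.9.
- PPC rate with no true difference: 10% to 60%, with PPC scored yes/no per patient.

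The article states no overall error rate and no power, so there is no planned figure to reproduce.

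**Step 1. Chance of a false primary claim under each possible rule**

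| Rule for success | Stated in the article? | Chance if neither outcome truly differs |
|---|---|---|
| PPC only | Suggested by Statistics | at most 0.05 (nominal) |
| Both required | No | at most 0.05 |
| Either one | Not stated, not excluded | 1 − 0.95² = 1 − 0.9025 = 0.0975 if independent |

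The either-one figure is 0.0975 / 0.05 = 1.95 times nominal. Whatever the correlation, it cannot exceed 0.05 + 0.05 = 0.10.

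**Step 2. Either-one rule with correlated tests** (bivariate normal, each test two-sided at 0.05)

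| Correlation | 0 | 0.3 | 0.5 | 0.7 | 0.9 |
|---|---|---|---|---|---|
| Chance of at least one false positive | 0.0975 | 0.0951 | 0.0907 | 0.0835 | 0.0704 |

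**Step 3. Either-one rule with the actual size of the PPC test.** With 20 per arm and a yes/no outcome, the PPC test does not have size exactly 0.05. Its exact size was found by enumerating all outcomes, then combined with an independent 0.05 test for PCT as 1 − (1 − size) × 0.95.
- *t* test, as Statistics specifies: size 0.039 to 0.053, giving 0.087 to 0.101. The top value occurs at a 30% PPC rate and reflects the discreteness of the data.
- Fisher's exact test, if used instead: size 0.0118 (10% rate) to 0.0248 (30% rate). This gives 1 − 0.9882 × 0.95 = 0.061 to 1 − 0.9752 × 0.95 = 0.074.

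**Step 4. The split results, read against the text**

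| Result | Statistics (PPC is primary) | Abstract and Study endpoints, either one counts |
|---|---|---|
| PPC null, PCT significant | Negative | Positive |
| PPC significant, PCT null | Positive | Positive |

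Only the first row depends on which section is followed.

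**The case against.** Four arguments can be made on the other side.

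*The error rate is not shown to be inflated.* A reader might infer that the false-positive chance is in fact doubled. The article does not support that. The figure needs the either-one rule, which no section states. With PPC alone as primary, or with both required, nothing is inflated. This objection stands, and the size has to be given as conditional.

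*A condensed article may leave the testing rule to a fuller document.* This is fair for the missing rule taken alone. It does not cover the mismatch: the article itself gives two primaries in two places and one in another, and it fixes the significance threshold. A later document could supply the rule, but the published sections would still have to be brought into line.

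*The parenthesis in Statistics may only identify which primary endpoint that sentence concerns.* This is possible. The following sentence gives PCT its own test, and Objectives of the study lists the two as separate numbered aims. On this view PCT has not been demoted, but then two primaries are each tested at 0.05 with no rule for combining them.

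*PPC and inflammation are related by the trial's own rationale, so independence overstates the figure.* This is partly right. No correlation is given, so the range is the proper statement, and even at 0.9 the either-one figure is about 7%.

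A reader might also infer that the opposite split, PPC significant and PCT null, is equally ambiguous. It is not. It is positive under Statistics and under the either-one reading. It would be negative only under a both-required rule, which no section states and which carries no inflation.

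**Conclusion.** The point holds as an internal mismatch with a conditional consequence. The Abstract and Study endpoints name two primary outcomes, Statistics attaches the label to PPC alone, and both are tested at an unadjusted 0.05 with no statement of what counts as success.

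If either result may count, the chance of a false primary claim could reach about 9.75% in place of 5%. That figure assumes independent tests of nominal size. It is about 7.0% to 9.5% for correlations of 0.9 to 0.3, and about 6% to 7.4% with Fisher's exact test for PPC at assumed rates of 10% to 60%. The text permits the either-one reading without stating it, so the increase is a possibility left open and not an established property of the plan. The ambiguity over PPC null with PCT significant needs none of these numerical assumptions.

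**What to change.** Make the Abstract, Study endpoints and Statistics agree before the data are analysed, in one of two ways.

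(a) Follow the label in Statistics. PPC is the single primary endpoint. PCT becomes the first secondary endpoint, tested for confirmation at 0.05 only if PPC is significant. PPC loses no power. The cost is that PCT cannot support a confirmatory claim when PPC fails, and that the endpoint wording in the Abstract and Study endpoints must change.

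(b) Keep both primaries and use Holm's procedure on PPC and one named PCT test, the group-by-time interaction of the repeated-measures ANOVA already planned. Compare the smaller *P* with 0.025 and, only if that is significant, the other with 0.05. The T0, T24 and T48 changes are then supportive. This holds the overall error at or below 0.05 whatever the correlation. It needs one added sentence in Statistics and a correction of the singular label.

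The cost of (b) is power for an endpoint judged at 0.025. For illustration only, since the article states no power: a test with 80% power at two-sided 0.05 has an expected *z* of 1.960 + 0.842 = 2.802. Against the 0.025 critical value of 2.241 the margin is 2.802 − 2.241 = 0.561 (rounded), which gives about 71%.

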### Blinding, data collection, randomization and record-keeping

This is a single-blinded (participant) study. Patient data, intraoperative and postoperative measurements, fluid balance, respiratory parameters, laboratory results and clinical status (Sequential Organ Failure Assessment (SOFA) score) will be collected onto Case Report Forms (CRF). CRF and the patient evaluation chart will not be assessed in front of the patient.

Participants will be randomized to the SG or CG in a ratio of 1:1. Randomization will be carried out by a computer-generated blocked randomization list with 10 blocks of four patients per block. Allocation will be stored in sealed, opaque and numbered envelopes. Participants will be included and allocated in numerical order.

All original records (CRF and relevant correspondence) will be archived and secured for 15 years, and then destroyed according to the hospital standards concerning destruction of confidential information.

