### Study arms and assigned intraoperative interventions

A total number of 40 patients with bladder cancer submitted to general anesthesia and open radical cystectomy and urinary diversion will be enrolled in this study. An equal number of patients will be randomized into the two groups.

Patients randomized into the SG group undergo an alveolar recruitment maneuver using the sustained airway pressure by the CPAP method, applying 30 cmH_2_O PEEP for 30 s followed by a decremental PEEP titration procedure directed by Cstat. During the PEEP titration procedure, PEEP will be decreased from 14 cmH_2_O by 2 cmH_2_O every 4 min, until a final PEEP of 6 cmH_2_O is reached. On each level of PEEP, ABGs will be collected and evaluated. Optimal PEEP is considered as the PEEP value resulting the highest possible Cstat measured by the ventilator. After the PEEP titration procedure, lung-protective mechanical ventilation will be performed using optimal PEEP and low tidal volumes and ARM will be performed every 60 min.

Patients randomized into the CG group will undergo an alveolar recruitment maneuver using the sustained airway pressure by the CPAP method, applying 30 cmH_2_O PEEP for 30 s followed by low-tidal-volume LPV using a PEEP value of 6 cmH_2_O and ARM will be repeated every 60 min.

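### The primary PPC definition gives a film or auscultation sign the same standing as ventilatory support, so a shift in severity can stay hidden within the endpoint

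*Protocol article*

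**What the plan says.** Under Study endpoints, "The primary outcome variables are PPC and PCT kinetics". The same section states that "PPC are defined as new infiltrates or atelectasis on a chest X-ray, abnormal breathing sounds on auscultation, respiratory failure", the last of these being PaO2/FiO2 < 300, or "the need for noninvasive or invasive ventilatory support within the first three postoperative days". It does not say whether PPC is counted once per patient, and it gives no order, weight or separate endpoint for any component.

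The Statistics section points two ways on scale:
- "Analysis of the primary endpoint (PPC) will be carried out by the unpaired Student’s" *t* test, which compares means.
- "Differences in proportions will be evaluated using the Fisher" exact test, with a risk ratio and its 95% CI.

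On size, "A total number of 40 patients with bladder cancer submitted to general anesthesia and open radical cystectomy and urinary diversion will be enrolled", and "Participants will be randomized to the SG or CG in a ratio of 1:1", so there are 20 patients per arm.

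**The concern.** The components run from a sign heard on auscultation to invasive ventilation. If they count alike, the PPC result can move for reasons that differ greatly in importance. Two results would be misread:
- fewer film or auscultation findings together with more ventilated patients, reported as fewer PPC or as no difference;
- equally frequent but milder PPC, reported as no effect.

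The mild items are also the most open to judgement. Only the participant is blinded. The chest X-ray has an independent reader, but none is stated for auscultation, and films after the first postoperative day depend on clinical suspicion. The trial sets out to assess possible disadvantages of the strategy as well as benefits, so the direction of the serious components matters.

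**Working it through.** **1. Does severity enter under any reading of the scale?**
- Any component per patient, compared as proportions: a film sign and invasive ventilation both score 1.
- *t* test on the same 0/1 values: this again compares two proportions.
- Count of components: each adds 1. A patient with a film sign and abnormal breath sounds scores 2, and a patient whose only recorded item is ventilatory support scores 1.

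Severity enters under none of them.

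**2. Is ventilatory support compared anywhere else?** Secondary endpoints are extrapulmonary, and their infection item leaves out pneumonia. Tertiary endpoints are ICU days, hospital stay and mortality. The adverse event definitions are tied to the PEEP titration procedure. No listed endpoint is ventilatory support.

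**3. Exact cancellation.** All rates here and below are assumptions, because the protocol gives none. With patients split into mild-only and ventilated, any PPC = mild-only + ventilatory support, and support rises from 5% to 15%:

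| Mild-only, control to study | Any PPC, control | Any PPC, study | Mild share of control events | Fisher rejects |
|---|---|---|---|---|
| 20% to 10% | 20 + 5 = 25% | 10 + 15 = 25% | 20/25 = 80% | 2.4% |
| 40% to 30% | 40 + 5 = 45% | 30 + 15 = 45% | 40/45 = 89% | 2.2% |
| 60% to 50% | 60 + 5 = 65% | 50 + 15 = 65% | 60/65 = 92% | 2.5% |

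The last column is exact enumeration at 20 v 20, two-sided 5%.

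**4. An apparent benefit with more ventilation.** Worst grade per patient (none / film or auscultation only / PaO2/FiO2 < 300 / noninvasive / invasive): control 25/60/10/3/2%, study 50/25/10/8/7%.
- Any PPC: 75% to 50%, risk ratio 50/75 = 0.67.
- PaO2/FiO2 < 300 or support: 15% to 25%, risk ratio 25/15 = 1.67.
- Ventilatory support: 5% to 15%, risk ratio 3.0.

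**5. Would a rank test on the worst grade solve this?** For the distributions in step 4:
- P(control worse) = 0.60×0.50 + 0.10×0.75 + 0.03×0.85 + 0.02×0.93 = 0.42.
- P(study worse) = 0.25×0.25 + 0.10×0.85 + 0.08×0.95 + 0.07×0.98 = 0.29.

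The rank test still leans towards the study arm. Its power at 20 v 20 (simulated; the binary tests are exact) depends on where the effect lies:

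| Control | Study | Binary test on any PPC | Rank test |
|---|---|---|---|
| 25/20/30/15/10 | 25/55/15/4/1 (large severity shift) | Fisher 2% | 37% |
| 25/20/30/15/10 | 25/35/25/10/5 (moderate shift) | Fisher 2% | 11% |
| 25/55/12/5/3 | 25/65/6/3/1 (mild-dominated, serious events halved) | Fisher 2% | 7% |
| 25/55/12/5/3 | 55/25/12/5/3 (only mild findings improve) | Fisher 38%, *t* test on 0/1 49% | 29% |

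**6. Precision of the serious components.** Fisher's test of 5% v 15% at 20 per arm has about 7% power. With 1/20 v 3/20 events the risk ratio is 3.0. The standard error of its log is √(1/1 − 1/20 + 1/3 − 1/20) = 1.11, giving a 95% CI of about 0.34 to 26.

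**The case against.** Four points can be made against the concern.

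- **The scale.** A reader might infer that PPC is settled as one yes/no event. The protocol never says so, and the *t* test suggests a mean. This stands: the scale is unresolved. The concern does not depend on it, because step 1 gives the same answer for every reading.
- **Which component dominates.** A reader might infer that mild findings decide the result. The documents do not show this. PaO2/FiO2 is calculated every 6 h to 72 h, about 72/6 = 12 chances to cross 300, while the X-ray is routine only on the first postoperative day, so PaO2/FiO2 < 300 could be the commonest component. Mild findings can decide the result; whether they will is unknown. For the same reason the serious subset could itself be driven by single threshold crossings, so ventilatory support should be shown alone as well.
- **Visibility of harm.** A reader might infer that harm would be invisible. That goes too far. Oxygenation is named beside PPC in the objectives, and serial PaO2/FiO2, daily SOFA, ICU days, stay and mortality are recorded. What stands is narrower: the shift is hidden within the PPC endpoint, and none of these is a comparison of ventilatory support.
- **Place in the documents.** Component tables are often left to an analysis plan, and none is shown, so their absence is not a fault in itself. The definition and the test named for PPC are stated in the article, however, and they are what create the problem.

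**Conclusion.** The concern holds in a limited form. The primary PPC definition ranks nothing, no stated reading of its scale lets severity in, and ventilatory support is not compared elsewhere. A change in severity, or an opposite change in ventilatory support, can therefore be hidden within PPC. Under the assumed rates, a tripling of support (5% to 15%) can leave any PPC unchanged, or sit beside a PPC risk ratio of 0.67.

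The calculations do not support replacing the primary analysis with a rank test. That test gains much when severity shifts strongly (37% v 2%), little when the shift is moderate or the endpoint is mostly mild (11% and 7%), and loses when only mild findings improve (29% v 38% for Fisher and 49% for a *t* test on 0/1). It also does not reliably expose opposing shifts. The step that exposes them is separate reporting of the serious components.

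All component rates, and a two-sided 5% level, are assumptions. This is an inexpensive improvement that should be made before analysis.

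**What to change.** Keep the components and the three-day window, and state before the data are analysed:
1. PPC is the occurrence of any component in a patient, compared as a proportion with a risk ratio and 95% CI, in place of the *t* test.
2. The serious subset (PaO2/FiO2 < 300 or ventilatory support), and ventilatory support alone, are each reported by arm with a risk ratio and 95% CI.
3. A PPC benefit is described as resting on mild findings if the serious subset does not point the same way.
4. As a supportive analysis, each patient's worst grade (0 none; 1 film or auscultation only; 2 PaO2/FiO2 < 300; 3 noninvasive support; 4 invasive support) is compared by the Mann-Whitney test, which the Statistics section already names.

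The cost is wording only, since the components must be ascertained per patient anyway. The ordering is a judgement and has to be agreed in advance. The subset results will be imprecise at 20 per arm and should be presented as descriptive.
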